## Governance and organizational structure

4.

INSIS is a global consortium focused on AEFIs and involving key clinical consultation services including the SIC Network, AEFI-CAN, members of the US Clinical Immunization Safety Assessment (CISA) network, Brighton Collaboration, GVDN, African Leadership in Vaccinology Expertise (ALIVE) network, experts in systems immunology (PVP, Boston Children’s Hospital; MVRG, OPBG, Rome, IT) and pharmacogenomics (University of British Columbia and BC Children’s Hospital Research Institute), and experts in pharmacogenomics and global vaccine policy (Global Healthcare Consulting and University of Washington). INSIS is managed by the Network Management Office (NMO) at the University of Alberta, under the leadership of the Nominated Principal Investigator (NPI) and Brighton Co-lead. The NMO coordinates operations, including finance, contracts, and communications, and interacts with the Task Force for Global Health, which hosts the Brighton Collaboration.

The Steering Committee, comprising representatives from key clinical networks and experts in vaccine safety and systems biology, oversees network governance, project progress, and funding. Monthly meetings facilitated by the NMO ensure alignment with project milestones. Specialized Working Groups, such as Data Management and OMICs, also meet monthly to support project deliverables. INSIS holds monthly calls open to all members to discuss and plan project progress and feature guest speakers on vaccine safety topics.

### Scientific advisory board and dissemination strategy

4.1.

INSIS will establish a Scientific Advisory Board (SAB) with diverse representation from funders, regulators, public health experts, and stakeholders, particularly from LMICs. The SAB will provide guidance on research priorities and ensure results are aligned with stakeholder needs and translated into policy.

INSIS will disseminate findings through its website, reports, presentations, open-access publications, and conferences. A Publication and Presentation Policy, following ICMJE guidelines, governs authorship and dissemination. Results will also be shared with participants and the public through institutional websites, media channels, and social media, with support from partner organizations’ communications teams.

## Conclusions

5.

The establishment of INSIS marks a significant advancement in the global effort to understand and mitigate rare AEFIs associated with COVID-19 vaccination. By integrating clinical data with advanced multi-omics technologies, INSIS provides a comprehensive platform for investigating the underlying mechanisms of AEFIs such as COVID vaccine-induced immune thrombocytopenia and thrombosis (VITT) and myocarditis. The rigorous data management and quality assurance processes employed by INSIS will ensure the accuracy and reliability of the collected data, facilitating robust analyses and meaningful conclusions. This approach will not only enhance our understanding of these conditions but also will inform vaccine development and development of personalized vaccination strategies, ultimately aiming to improve public health outcomes.

As the work progresses and the network continues to expand, INSIS aims to apply the methodology described herein to new AEFIs and additional vaccines targeting diverse threats. INSIS’ collaborative framework and cutting-edge methodologies will remain crucial in addressing emerging vaccine safety signals. INSIS’s efforts highlight the importance of global collaboration in vaccine safety research and emphasize the potential of integrating clinical, immunologic, and multi-omics analysis to drive scientific discoveries and inform public health policies.

**Fig. 2. F2:**
[figure not shown]
The International Network of Special Immunization Services (INSIS) approach to defining biomarkers of vaccine-associated adverse events. A) AEFI cases and controls are recruited. B) Cases and controls undergo standard assessment, data and sample are collected at INSIS clinical assessment centers. C) Data are transferred to the INSIS central database, and samples are processed at INSIS laboratories for multi-OMICs. D) Integration and analysis of clinical and biological data. E) Biomarkers that predict or correspond to AEFIs will be identified. F) Results will inform vaccine development and personalized vaccination strategies. Abbreviation: AEFI, adverse event following immunization.

**Fig. 3. F3:**
[figure not shown]
INSIS Sample Processing Pipeline and Core Lab assays. A) The following assay prioritization will be used for retrospective samples: Serum samples will be used to measure metabolomics, proximity extension assay proteomics (Olink), antigen array, proteomics, and hormone analysis. Plasma will be used to measure cytokines and chemokines, proteomics, Olink, human in vitro modeling and hormone analysis. PBMCs will be used for RNAseq or transcriptomics analysis, epigenetics, human in vitro modeling, immunophenotyping using mass cytometry time of flight (CyTOF) and ELISPOT. Saliva will be used for genomics and RNA for transcriptomics analysis. B) For prospective samples; whole blood collected in tubes with an anticoagulant (EDTA preferably) will be processed for PBMCs and plasma samples. Serum will be collected in tubes without any anticoagulant (e.g. SST Greiner tubes). Saliva will be used for genomics. The retrospective samples processing pipeline will be followed for all prospective sample types. Core Labs: Boston Children’s Hospital (BCH), Clinical and Research Unit of Clinical Immunology and Vaccinology, Bambino Gesù Children’s Hospital (Bambino), Mayo Clinic College of Medicine (Mayo), University of British Columbia (UBC).

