VITT has been linked to adenoviral vector COVID-19 vaccines (e.g., ChAdOx1 and Ad.26.COV-2.S). First reported in March 2021, VITT is characterized by rapidly progressive thrombosis, particularly in cerebral venous sinuses and splanchnic circulation veins, accompanied by thrombocytopenia and markedly elevated D-dimer and anti-platelet factor 4 (PF4) antibodies driving platelet activation [11-15]. The incidence of VITT ranges from 0.1 to 1.2 cases per 100,000 vaccinations following Ad26.COV-2.S and 1 to 5 per 100,000 following the first dose of ChAdOx1 vaccine [16]. Early diagnosis and treatment have reduced case fatality rates from as high as 40 % to 13–15 % [17].

Myocarditis and pericarditis emerged as safety signals following the rollout of COVID-19 mRNA vaccines. Although these vaccines have been pivotal in controlling the pandemic, there is an increased incidence of myocarditis and pericarditis, particularly among young males aged 12–29 years after the second dose [18,19-25]. Initial data suggested most patients appeared to recover quickly. Ongoing studies are focused on determining long-term outcomes, including resolution of cardiac MRI changes and cardiac-specific biomarkers, with some studies reporting persistence of MRI changes and symptoms in a subset of patients [26]. Importantly, despite these rare events, the benefits of COVID-19 vaccination in preventing severe disease, hospitalization, and death continue to far outweigh the risks. The mRNA platform is now being used to develop vaccines against a range of other diseases including influenza, Respiratory Syncytial Virus (RSV), Nipah, and Lassa fever, as well as for non-infectious indications such as cancer [11,27].

Myocarditis and pericarditis have also been reported following non-mRNA COVID-19 vaccines, including the adjuvanted protein subunit vaccine Novavax NVX-CoV2373 and AstraZeneca’s ChAdOx1 [23]. Early studies suggest that the spike protein may contribute to these rare cardiac events [28,29]. Ongoing research into the underlying biological mechanisms is essential to refine our understanding of vaccine safety. Continued surveillance and investigation are critical to ensuring public confidence and the safety of vaccination programs.

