#### Untargeted mass spectrometric profiling

2.5.1.

Proteomics will be performed ([name] Lab, Boston Children’s Hospital; Boston, MA) employing a two-pronged approach [42]. First, the plasma proteome will be quantitatively mapped without any depletion considering the important immunomodulatory roles of a sizable fraction of the standard depletion targets such as immunoglobulins and complement pathway components [43,44]. Mapping the vaccine and AEFI-associated changes in abundance for these proteins is important for understanding the pathophysiological processes of these AEFIs. To map the ‘classical’ plasma proteome, the neat plasma will be processed in a high throughput fashion. To map the ‘tissue leakage’ plasma proteome, we will deplete the most abundant plasma samples using perchloric acid, which can be conducted in a high-throughput and cost-efficient manner on thousands of samples [45-47].

The two resulting plasma protein digests will be analyzed by LC-MS in discovery mode using a high-throughput sample delivery and high-performance liquid chromatography (HPLC) system (Evosep One) front-end and a Bruker ion mobility/quadrupole/TOF mass spectrometer (timsTOF HT) back-end to ensure robustness. The instrument will be operated in Data Independent Acquisition (DIA) mode to ensure maximum completeness of the data. All data will be qualitatively and quantitatively analyzed using the Bruker ProteoScape hard- and software environment.

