#### Untargeted metabolomics profiling

2.5.3.

Metabolomics offers a powerful tool for understanding vaccine safety events by providing comprehensive insights into the biochemical changes associated with vaccination. By detecting specific and consistent metabolic signatures, metabolomics allows for the precise identification of disease states or vaccine responses [49]. For example, alterations in prostaglandin metabolites and eicosanoids, related to hyperinflammation, may help pinpoint the biochemical basis of adverse reactions [50]. Additionally, metabolic dysregulation has been observed in COVID-19 hospitalized patients with severe disease trajectories, including decreased phospholipid components and elevated plasma branched-chain amino acid (BCAA) and urea components captured by untargeted metabolomics [51]. Furthermore, integrating metabolomics with other systems biology platforms can provide a holistic view of the host immune response [49].

Plasma metabolomics assay for the INSIS project will be conducted (Metabolon, Durham, NC) using a previously described workflow [49]. Samples will be randomized into batches, extracted, and prepared for analysis using solvent extraction method [52]. Recovery standards will be added at the initial extraction step to ensure quality control. Proteins will be precipitated with methanol under vigorous shaking and then centrifuged. The resulting supernatants will be divided into five fractions for various analyses, including two reverse phase (RP)/UPLC-MS/MS methods with positive ion mode electrospray ionization (ESI), one RP/UPLC-MS/MS with negative ion mode ESI, one HILIC/UPLC-MS/MS with negative ion mode ESI, and one reserved for backup analysis using high-resolution mass spectrometry. Metabolites will be identified by comparing results to a library of standard metabolites [52] using criteria such as retention index, accurate mass match, and MS/MS scores. Compounds will be categorized according to standards set by the Metabolomics Standards Initiative [53-55]. Appropriate analytical techniques will be used to validate and report metabolites of interest, ensuring accurate and reliable data for further analysis.

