### Integrated multi-omics analysis

3.5.

Multi-omics data from patients with well-defined phenotypes (e.g., Brighton level 1 TTS/VITT) and controls will be analyzed using data integration approaches such as MultiOmics Factors Analysis (MOFA) and Data Integration Analysis for Biomarker Discovery using Latent Components (DIABLO) as previously described [84,85]. MOFA is a computational method used to integrate and analyze multi-omics datasets which distinguishes between patterns that are shared across different omics layers and those that are specific to individual layers [84]. DIABLO identifies key drivers associated with the response variable of interest across all input data matrices jointly. Cross-validation will determine the optimal model hyperparameters (number of components, features per component) and estimate the model’s ability to generalize to new data. Selected model features will undergo pathway over-representation analysis against the Reactome pathways database (via MSigDB) and blood transcriptional module (BTM) annotated gene set libraries, with *p*-values adjusted to control false discovery rate (FDR).

Multi-omics data will be compared within groups over time (e.g., myocarditis/TTS/VITT onset vs post-recovery) and between cases and controls to identify differences in basal levels of analytes in cases (using baseline samples: pre-vaccination, post-recovery/ ≥3 months postvaccination), as well as at time of myocarditis/TTS/VITT diagnosis (and similar timepoints post-vaccination in controls). Analyte levels in blood/plasma will also be compared to normal ranges in adults where available. Two-way comparisons will be performed between cases and healthy controls vs cases and controls with non-vaccine associated myocarditis or HIT.

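### Fig. 3 and the methods text disagree on serum versus plasma; in serum, mostly platelet-released analytes may follow platelet count in two TTS/VITT contrasts

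*Protocol article*

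**What the plan says.** The Fig. 3 caption assigns assays to sample types. For serum: "Serum samples will be used to measure metabolomics, proximity extension assay proteomics (Olink), antigen array, proteomics, and hormone analysis". For plasma: "Plasma will be used to measure cytokines and chemokines, proteomics, Olink, human in vitro modeling and hormone analysis". So metabolomics is listed for serum only, and Olink and proteomics for either matrix. Part B of the caption carries this forward: "The retrospective samples processing pipeline will be followed for all prospective sample types".

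The methods text differs. Section 2.5.1, on mass-spectrometric proteomics, says: "First, the plasma proteome will be quantitatively mapped without any depletion". Section 2.5.3 says: "Plasma metabolomics assay for the INSIS project will be conducted (Metabolon, Durham, NC) using a previously described workflow". Section 2.5.2 allows Olink on either plasma or serum.

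The Introduction describes VITT as thrombosis "accompanied by thrombocytopenia and markedly elevated D-dimer and anti-platelet factor 4 (PF4) antibodies driving platelet activation". Section 2.4.2 compares these cases with healthy vaccinated controls and with controls who have non-vaccine-associated TTS/VITT-like conditions. Section 3.5 adds a comparison over time: "Multi-omics data will be compared within groups over time (e.g., myocarditis/TTS/VITT onset vs post-recovery) and between cases and controls". The matching factors in Section 2.4.3 are age, sex, vaccine and ancestry. Neither sample matrix nor platelet count is among them.

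**The concern.** There are two linked problems. The first is internal: for metabolomics, Fig. 3 and Section 2.5.3 name different matrices, so a laboratory or site could follow either and claim to follow the protocol.

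The second is why the choice is not neutral for TTS/VITT. Serum is made by letting blood clot in the tube. Clotting platelets release granule contents and form eicosanoids, so the measured level is the circulating level plus an amount added in the tube. That added amount depends on how many platelets were present. A low platelet count is part of the TTS/VITT definition. It is absent in healthy controls and should have resolved in the case's own recovery sample. Using serum throughout a contrast does not remove the difference, because the artefact comes from the platelets and not from mixing matrices.

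The exposed analytes matter to the study. The Introduction gives platelet activation as the VITT mechanism, and Section 2.5.3 says that "alterations in prostaglandin metabolites and eicosanoids, related to hyperinflammation, may help pinpoint the biochemical basis of adverse reactions". At stake is a platelet-count effect reported as a molecular signature. An integrative method such as DIABLO could then select it, because the affected features would move together across the protein and metabolite layers.

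**Working it through.** **Step 1: the matrices side by side.**

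| Assay | Fig. 3 | Methods text |
|---|---|---|
| Metabolomics | serum only | plasma (2.5.3) |
| Mass-spectrometric proteomics | serum and plasma | plasma (2.5.1) |
| Olink | serum and plasma | plasma or serum (2.5.2) |
| 41-plex cytokines/chemokines | plasma only | plasma (2.8) |

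Metabolomics is a direct contradiction. Proteomics is wider in the figure than in the text. Olink is open in both places. The 41-plex panel is consistent.

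**Step 2: a simple model for serum.** The documents give no figure for release on clotting, so there is no plan figure to reproduce and every input here is an assumption. Let

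- f = share of the control's serum level that platelets release during clotting;
- g = true circulating case/control ratio;
- r = case/control ratio of platelet counts.

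If release is proportional to platelet count,

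serum case/control ratio = (1 − f)·g + f·r.

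For g > 1 the serum ratio falls below 1, a reversed sign, when f > (g − 1)/(g − r). The same identity serves for onset versus recovery if the recovered count is taken as the reference.

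**Step 3: no true difference (g = 1), r = 0.2.**

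- f = 0.05: 0.95 + 0.01 = 0.96
- f = 0.50: 0.50 + 0.10 = 0.60
- f = 0.95: 0.05 + 0.19 = 0.24

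With a healthy count of 250 and onset counts of 20 to 100 (×10⁹/L), r runs from 20/250 = 0.08 to 100/250 = 0.40. The ratio then runs from 0.5 + 0.5 × 0.40 = 0.70 (f = 0.50, count 100) down to 0.05 + 0.95 × 0.08 = 0.13 (f = 0.95, count 20).

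**Step 4: a true doubling in the circulation (g = 2).** At r = 0.2 the reversal threshold is (2 − 1)/(2 − 0.2) = 0.556. Over r = 0.1 to 0.6 it is 0.526 to 0.714. For counts of 20 to 100:

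| f | Serum ratio, count 20 (r = 0.08) | Serum ratio, count 100 (r = 0.40) |
|---|---|---|
| 0.50 | 1.04 | 1.20 |
| 0.60 | 0.85 | 1.04 |
| 0.90 | 0.27 | 0.56 |

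At half clot-released, the doubling is nearly hidden but keeps its sign. At 90%, it is reversed. At f = 0.05 and r = 0.2 it reads 1.91, which is almost unbiased.

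**Step 5: would the artefact be detected as a finding?** Assume 20 cases and 20 controls, log-scale SD 0.5 and a two-sample t test.

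| Spurious ratio | Power at 0.05 | Power at 0.05/1000 |
|---|---|---|
| 0.28 | above 99% | 99.9% |
| 0.60 | 88% | 12% |
| 0.70 | 59% | 2% |

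A strong artefact would pass a strict multiplicity threshold; a moderate one usually would not.

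**The case against.** The strongest reply is that the protocol already intends plasma. Sections 2.5.1 and 2.5.3 say so, and the same caption lists proteomics and Olink under plasma. A reader who takes only the serum sentence might infer that all three platforms run on serum. The documents do not support that, and this part of the reply stands. What remains is that the caption gives metabolomics no plasma route, offers serum as an equal route for the other two, and applies this to new samples as well as old ones.

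A reader might also infer that case-control differences in these assays simply reflect platelet count, with the wrong sign. That goes too far. Steps 3 and 4 show that both the deficit and the reversal depend on the clot-released share, which the documents do not give. The growth factors that come first to mind (PDGF, sCD40L, EGF, RANTES) are in the 41-plex panel of Section 2.8, which uses plasma. The protocol does not say which Olink panels will be run, and it offers eicosanoids as an example, not as an endpoint.

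The scope is also limited. Nothing here concerns myocarditis or pericarditis. HIT and TTS-like controls are thrombocytopenic too, so those comparisons are largely protected. Section 2.4.4 allows sampling up to 12 weeks after the event, so not every case sample will have a low count.

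Finally, Section 2.4.4 refers to a sample SOP that is not shown, and serum may be all that survives for rare retrospective cases. Both points are fair. They bear on how serum-only participants are handled, but they do not settle which matrix the protocol names.

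**Conclusion.** The contradiction is established from the protocol alone: metabolomics is serum in Fig. 3 and plasma in Section 2.5.3, and Fig. 3 opens a serum route for proteomics that Section 2.5.1 does not describe.

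The bias is conditional. It rests on platelets releasing material on clotting roughly in proportion to their number, which is general biology and not in the documents, and on assumed values of f, g and r. Under those assumptions, mostly platelet-released analytes measured in serum may be dominated by platelet count in the TTS/VITT case-versus-healthy and onset-versus-recovery contrasts. The spurious ratio is 0.60 at f = 0.50 and r = 0.2, and a true doubling reverses sign only above f of about 0.56. A general claim of wrong signs across these platforms is not supported. The point deserves action now because collection is continuing and serum cannot later be turned into plasma.

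**What to change.** Correct Fig. 3 so that metabolomics and mass-spectrometric proteomics agree with Sections 2.5.1 and 2.5.3. For TTS/VITT sets and their comparators, state that metabolomics, mass-spectrometric proteomics and Olink use plasma wherever it exists, with one matrix within each contrast. Keep serum for the antigen array.

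Where only serum exists, flag the platelet-release analytes and interpret them mainly against thrombocytopenic disease controls such as HIT. Use the platelet count nearest the draw in a sensitivity analysis. A fixed exclusion list or a compulsory covariate in the main analysis is not needed, and a fixed exclusion would fit poorly with the study's open discovery aim.

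The cost is figure and SOP wording plus one sensitivity analysis. The downside is small: serum-only TTS/VITT participants contribute less to the case-versus-healthy and onset-versus-recovery contrasts.

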**Fig. 4. F4:**
[figure not shown]
INSIS Sample and Data Management Pipeline. This figure illustrates the comprehensive workflow for sample and data management within the INSIS study. Data collection is performed at various clinical sites, involving the development of standard operating procedures (SOPs), as well as sample processing and preparation. The map illustrates the global locations of these clinical sites. Collected clinical data are harmonized and standardized by the Data Management Working Group (DMWG) using the REDCap platform, in collaboration with the Brighton Collaboration and the Safety Platform for Emergency Vaccines (SPEAC). A rigorous quality control (QC) and quality assurance (QA) process ensures the accuracy and reliability of both data and samples before analysis. Specialized core sites conduct various assays and omics analyses, including transcriptomics, Cytometry by Time-Of-Flight (CyTOF), Proximity Extension Assay (PEA) for cytokine profiling (Olink), metabolomics, proteomics, cytokine/chemokine analysis, genomics, antigen array analysis, and in vitro stimulation assays. The pipeline includes meticulous sample coordination, tracking, and shipment to ensure samples are handled and processed correctly. Single and multi-omics data are analyzed and integrated within a centralized computing environment, facilitating comprehensive data interpretation and manuscript preparation. Final datasets and associated metadata are deposited in public repositories such as NCBI Gene Expression Omnibus (GEO) and ImmPort, ensuring data accessibility for the broader research community.

**Table 1 T1:** Schedule of study procedures, prospectively enrolled cases and controls for multi-OMICs analysis. *†, ‡

	During adverse event/onset myocarditis/VITT/TTS	2–8 weeks after event onset†	~12–20 weeks after onset	~6–24 months after onset
Cases and controls with non-vaccineassociated disease	Consent (if possible) Data collection Blood collection*	Consent‡ Data collection Blood collection	Consent (if not yet obtained) ‡ Data collection Blood collection	Data collection Blood collection
	Pre-vaccination (if available)	~3–90 days post vaccination**	~12–20 weeks post vaccination	~6–24 months post vaccination
Controls	Consent (if possible) Data collection Blood collection**	Consent‡ Data collection Blood collection	Consent (if not yet obtained) ‡ Data collection Blood collection	Data collection Blood collection

* Participants may be included if multi-OMICs samples are available from only 1 timepoint but 2 or more timepoints are preferred within these approximate timeframes (preferably an acute sample and follow up sample). In some cases an early follow up sample and late follow up sample (e.g., 3 and > 6 months) will be acceptable. A maximum of 90 ml of blood will be drawn on children <16 years of age.

† At time of first specialist assessment (e.g., cardiology, special immunization clinic).

‡ If not consented at presentation, consent will be obtained at time of specialist assessment for retrieval of residual serum/plasma from initial presentation.

** Aim for 3–7 days post-vaccination for controls matched to myocarditis cases; 5–42 days post-vaccination for controls matched to VITT cases, longer timeframes may be appropriate for additional AEFI of interest.

